## Abstract

**Background:**

Primary biliary cholangitis (PBC) management remains limited by reliance on static biochemical markers, fragmented assessment of symptom burden, and inadequate noninvasive risk stratification for clinically significant portal hypertension (CSPH). Existing tools fail to integrate longitudinal laboratory trends, elastography, and patient-reported outcomes, and translation of risk assessment into guideline-concordant clinical action remains inconsistent.

**Objective:**

This study aims to develop, validate, and pilot an explainable artificial intelligence (AI) framework—AIm-PBC—for continuous disease monitoring, early prediction of CSPH complications, and delivery of guideline-based clinical decision support in patients with PBC.

**Methods:**

We will conduct a multiphase study combining retrospective cohort analysis, prospective observational data collection, and implementation evaluation. At least 600 adults with confirmed PBC will be enrolled across academic hepatology centers. The AI framework will integrate longitudinal biochemical markers, noninvasive elastography metrics, and high-frequency patient-reported outcomes to generate an interpretable disease activity index and predict CSPH-related complications using gradient-boosted models with Shapley additive explanations. Outputs will be deployed via a SMART-on-FHIR (Substitutable Medical Applications, Reusable Technologies on Fast Healthcare Interoperability Resources)–enabled electronic health record clinical decision support tool. Implementation will be evaluated using a randomized crossover simulation followed by a pragmatic pilot assessing usability, cognitive load, clinician adherence, and feasibility.

**Results:**

The primary outcomes include calibration and responsiveness of the disease activity index; discriminatory performance of the CSPH prediction model compared with established criteria; and effectiveness of the decision support tool measured via improvements in guideline-concordant care, usability scores, and clinician cognitive workload. Secondary outcomes include fairness metrics and workflow efficiency.

**Conclusions:**

This protocol outlines a scalable, explainable AI framework designed to bridge gaps between disease monitoring, risk prediction, and clinical action in PBC. If successful, AIm-PBC may enhance early complication detection, improve symptom management, and support equitable, evidence-based care delivery in routine hepatology practice.

## Introduction

### Background

Despite advances in primary biliary cholangitis (PBC) therapy, significant gaps persist in monitoring disease activity, predicting complications, and delivering guideline-concordant care [1-4]. Current management strategies rely heavily on biochemical markers such as alkaline phosphatase (ALP) and bilirubin, which often fail to capture dynamic symptom fluctuations or early progression toward clinically significant portal hypertension (CSPH) [5,6]. This limitation delays timely intervention and contributes to morbidity [7].

Risk stratification for portal hypertension, a complication of PBC, remains particularly challenging [8]. Invasive procedures such as endoscopy are frequently used for variceal screening, yet these approaches are resource intensive and carry procedural risks [2,4]. Noninvasive surrogates, including liver stiffness measurement (LSM) and spleen stiffness measurement (SSM), have demonstrated promise in predicting CSPH and reducing unnecessary endoscopies [2,4,9]. However, these modalities are rarely integrated with longitudinal biochemical data or patient-reported outcomes (PROs), leaving clinicians without a comprehensive, real-time view of disease trajectory [10]. Even when risk is identified, translating insights into action remains challenging. Clinicians face cognitive overload and workflow fragmentation, leading to missed opportunities for guideline-based interventions such as pruritus step therapy, bone health management, and CSPH screening [3].

Symptom burden represents another critical dimension of PBC care. Validated instruments such as the Worst Itch Numeric Rating Scale (WI-NRS) and PBC-40 provide reliable measures of symptom severity [10,11]. Similarly to risk stratification tools, symptom burden tools are underused in routine practice and seldom incorporated into predictive models.

### Proposed Solution

Artificial intelligence (AI) offers an opportunity to address these gaps by integrating heterogeneous data streams, including biochemical markers, elastography metrics, and PROs, into dynamic, explainable models capable of continuous monitoring and risk prediction [12-14]. By developing an agentic AI system that integrates longitudinal biochemical data, elastography metrics, and high-frequency PROs, we aim to provide clinicians with a dynamic, explainable disease activity index. This approach will enable proactive management of symptoms and early identification of nonresponders [15], reducing morbidity and improving patient-centered outcomes. Our multi-signal predictive model will integrate elastography, platelet count, biochemical response, and comorbidity profiles to accurately identify patients at high risk of early CSPH complications. This composite approach promises to reduce unnecessary endoscopies while ensuring timely prophylaxis for those at greatest risk. By embedding explainable AI outputs into an electronic health record (EHR)–integrated clinical decision support (CDS) tool, we aim to bridge the gap between prediction and practice. This prototype will feature interpretable risk cards and dual-threshold triage cues, ensuring usability and trust while promoting equity across diverse clinical settings. While machine learning algorithms have shown promise in chronic liver disease, most operate as “black boxes,” limiting clinician trust and adoption. Consequently, we aim to use Shapley additive explanations (SHAP) combined with dual-threshold triage strategies to enhance transparency and usability.

### Study Aim

This protocol describes a multiphase study designed to develop, validate, and pilot this explainable AI framework for PBC management. The proposed framework, named AIm-PBC system, will integrate longitudinal multi-signal data to (1) provide continuous, interpretable assessment of disease activity and symptom burden; (2) predict CSPH complications using a composite noninvasive model; and (3) operationalize guideline-concordant care through an EHR-integrated CDS prototype (Figure 1). By leveraging implementation science principles, this study aims to ensure feasibility, usability, and equity across diverse clinical environments.

**Figure 1. F1:**
[figure not shown]
Conceptual framework for the explainable artificial intelligence (AI) system for symptom and disease monitoring, early portal hypertension prediction, and remote clinical decision support (CDS) in primary biliary cholangitis (PBC). ALP: alkaline phosphatase; AQFIB-4: Fibrosis-4 index for liver fibrosis; CSPH: clinically significant portal hypertension; DO: doctor of osteopathic medicine; EHR: electronic health record; MD: doctor of medicine; NP: nurse practitioner; PA: physician assistant.

### Hypothesis

We hypothesize that this integrated, explainable AI approach will outperform conventional monitoring strategies, improve risk stratification for CSPH, and enhance clinician adherence to evidence-based care pathways, ultimately reducing symptom burden and preventing complications in patients with PBC.

### Study Setting

The study will be conducted across multiple hepatology clinics affiliated with academic medical centers in the United States. The CDS pilot will be implemented within EHR environments supporting SMART-on-FHIR (Substitutable Medical Applications, Reusable Technologies on Fast Healthcare Interoperability Resources) integration.

### Eligibility Criteria

Adults aged 18 years or older with a confirmed diagnosis of PBC according to American Association for the Study of Liver Diseases criteria (ie, defined as elevated ALP of ≥1.5 times the upper limit of normal in combination with a positive antimitochondrial antibody or disease-specific antinuclear antibodies such as sp100 or gp210) [2]. For individuals who are seronegative, histological confirmation through liver biopsy will be mandatory. All participants must have been receiving standard therapeutic dosing of ursodeoxycholic acid for a minimum of 3 months prior to enrollment, defined as 13 to 15 mg per kilogram of body weight per day administered in 2 or 3 divided doses [2]. Patients who are on second-line therapies, including farnesoid X receptor agonists or peroxisome proliferator–activated receptor agonists, will also be eligible, and therapy class will be recorded as a covariate. Additionally, baseline elastography data, including LSM and SSM, must be available within 6 months of enrollment.

Individuals will be excluded if they have previously undergone liver transplantation or are currently listed for transplantation or if they present with decompensated cirrhosis at baseline, defined as Child-Pugh class B or C [16]. Other exclusion criteria include active malignancy, uncontrolled systemic illness, pregnancy, or inability to provide informed consent. Patients with significant alcohol consumption within 6 months of enrollment (ie, more than 20 grams per day for female individuals or more than 30 grams per day for male individuals or an Alcohol Use Disorders Identification Test–Consumption score of 4 or higher) [17] will not be eligible. Additional exclusions are coexisting chronic liver diseases such as chronic viral hepatitis, hemochromatosis, Wilson disease, or alpha-1 antitrypsin deficiency, as well as active or suspected drug-induced liver injury within the prior 6 months, including drug-induced autoimmune hepatitis (AIH). Any condition deemed by the investigators to compromise participant safety or data integrity will also result in exclusion. A summary of inclusion and exclusion criteria is provided in Textbox 1.

To enable subgroup analyses, participants will be stratified by the presence of AIH overlap, defined using the Paris criteria [18], and by the presence of metabolic dysfunction–associated steatohepatitis (MASH), identified through structured chart abstraction and imaging or laboratory features [19-21]. Stratification will also occur based on biochemical response status at 12 months following initiation of ursodeoxycholic acid therapy, categorized using established UK-PBC and GLOBE risk scores [22,23].

Textbox 1.Inclusion and exclusion criteria.
**Inclusion criteria**
Adults aged ≥18 yConfirmed diagnosis of primary biliary cholangitis according to American Association for the Study of Liver Diseases criteria, defined as elevated alkaline phosphatase of ≥1.5 times the upper limit of normal with positive antimitochondrial antibody or disease-specific antinuclear antibodies such as sp100 or gp210 [2]For seronegative individuals, histological confirmation via liver biopsyReceiving standard therapeutic dosing of ursodeoxycholic acid for ≥3 mo before enrollment, defined as 13 to 15 mg per kilogram per day in 2 or 3 divided doses [2]Patients receiving second-line therapies, including farnesoid X receptor agonists or peroxisome proliferator–activated receptor agonists, with therapy class recorded as a covariateBaseline elastography data, including liver stiffness measurement and spleen stiffness measurement, available within 6 mo of enrollment
**Exclusion criteria**
Prior liver transplantation or currently listed for liver transplantationDecompensated cirrhosis at baseline, defined as Child-Pugh class B or C [16]Active malignancy, uncontrolled systemic illness, pregnancy, or inability to provide informed consentSignificant alcohol consumption within 6 mo of enrollment, defined as >20 g per day for female individuals or >30 g per day for male individuals or Alcohol Use Disorders Identification Test–Consumption score of ≥4 [17]Coexisting chronic liver diseases, including chronic viral hepatitis, hemochromatosis, Wilson disease, or alpha-1 antitrypsin deficiencyActive or suspected drug-induced liver injury within the prior 6 mo, including drug-induced autoimmune hepatitisAny condition deemed by the investigators to compromise participant safety or data integrity

### Interventions

The intervention consists of the development and deployment of the AIm-PBC framework across 3 sequential phases. The first phase focuses on building an agentic AI system capable of continuous monitoring of disease activity and symptom burden. This system will integrate multiple data streams, including monthly biochemical markers, periodic elastography measurements such as LSM and SSM, and high-frequency PROs collected through validated instruments such as the WI-NRS and the PBC-40. The agent will autonomously orchestrate data ingestion, normalization, and analysis to generate an explainable disease activity index supported by SHAP-based visualizations to ensure interpretability for clinicians.

The second phase involves the creation and validation of a multi-signal predictive model for early identification of portal hypertension complications. This model will combine elastography metrics, platelet count, biochemical response trajectories, and comorbidity profiles, including AIH and MASH overlap. By leveraging gradient-boosted ensemble algorithms and explainability frameworks, the model aims to outperform existing single-modality rules and consensus criteria such as Baveno VII [24], providing a noninvasive, accurate method for triaging endoscopy referrals and initiating prophylactic interventions.

The third phase operationalizes these insights through an EHR-integrated CDS prototype. Built within a SMART-on-FHIR architecture, the CDS tool will present clinicians with interpretable risk cards; dual-threshold triage cues; and guideline-based order sets for interventions such as pruritus step therapy, bone health management, and endoscopy referral. This phase includes a randomized crossover simulation to evaluate usability, decision accuracy, and cognitive load, followed by a pragmatic pilot in hepatology clinics to assess feasibility and effectiveness in real-world workflows. Collectively, these interventions aim to transform PBC care by embedding explainable AI into routine practice, improving monitoring, risk prediction, and adherence to evidence-based management strategies.

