### Outcomes

The primary outcome for the first aim will be the performance of the AIm-PBC disease activity index compared to conventional monitoring strategies. This will be assessed through its calibration against established risk scores such as UK-PBC and GLOBE [22,23], as well as its responsiveness to clinically meaningful changes in disease activity. The ability of the integrated symptom indexes to correlate with biochemical progression or regression will also be evaluated, providing insights into whether the inclusion of PROs enhances the sensitivity of disease monitoring. Explainability will be measured via the interpretability of SHAP-based visualizations and their perceived clinical utility during clinician evaluations.

For the second aim, the primary outcome will be the discriminatory ability of the multi-signal predictive model to identify patients at high risk of CSPH and early complications such as variceal hemorrhage or ascites. This will be quantified using the area under the receiver operating characteristic curve (AUROC), with additional measures of calibration and clinical utility assessed through decision curve analysis and net reclassification improvement. Comparative analyses will determine whether the composite model outperforms single-modality rules and consensus criteria such as Baveno VII, and subgroup analyses will explore performance consistency across patients with AIH overlap and MASH.

For the third aim, the primary outcome will be the effectiveness and usability of the EHR-integrated CDS prototype. Effectiveness will be measured via improvements in clinician adherence to guideline-concordant care pathways, including pruritus management, bone health interventions, and risk-based endoscopy referrals. Usability will be assessed using the System Usability Scale, with a target score of 70 or higher, and cognitive load will be evaluated using the NASA-Task Load Index. Clinician trust in the AI system will be measured through the AI trust scale, whereas decision accuracy and decision time will be compared between CDS-assisted and usual care conditions during the randomized crossover simulation. Feasibility indicators, including recruitment and completion rates, will be monitored during the pragmatic pilot phase.

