### Data Collection

Retrospective data will be sourced from institutional EHRs and data warehouses, capturing historical laboratory values, elastography reports, and clinical outcomes relevant to PBC. Prospective data collection will be conducted in outpatient hepatology clinics using secure, HIPAA (Health Insurance Portability and Accountability Act)-compliant platforms such as REDCap for PROs. These outcomes will include validated instruments such as the WI-NRS, administered twice daily to capture circadian variation in pruritus, and the PBC-40 questionnaire, administered monthly to assess quality of life domains.

Biochemical data, including ALP, bilirubin, aminotransferases, albumin, and platelet count, will be collected at monthly intervals to provide high-resolution longitudinal trajectories. LSM and SSM values will be obtained at baseline and during scheduled follow-up visits, with probe frequency and stiffness values recorded in kilopascals to ensure standardization. Clinical outcomes such as time to variceal development, ascites, and hepatic encephalopathy will be tracked over a 24-month observation period.

All data will be deidentified prior to analysis and stored in secure environments that comply with institutional and federal privacy regulations. Quality control procedures will include automated range checks for laboratory values, standardized reporting templates for elastography, and audit trails for PRO completion. Missing data will be addressed using multiple imputation techniques to minimize bias and preserve statistical power. Data integration will occur through structured pipelines that normalize heterogeneous inputs for use in machine learning models, ensuring consistency across biochemical, imaging, and symptom domains.

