### AI Model Development and Validation

The predictive model will be developed using a prespecified machine learning pipeline. Candidate predictors will include longitudinal biochemical markers, platelet count, LSM, SSM, symptom scores, treatment response status, and relevant comorbidities. Features will be selected based on clinical relevance, data availability, and model stability, with highly collinear or sparsely available variables excluded or combined where appropriate.

The dataset will be divided into training, internal validation, and held-out testing subsets at the patient level to avoid data leakage. Model development will use gradient-boosted ensemble algorithms, with hyperparameters tuned within the training set using cross-validation. External validation will be performed using data from at least one participating site not used during model training where feasible.

Class imbalance will be addressed using strategies applied only within the training data, including class weighting or resampling approaches as appropriate. SHAP values will be generated to provide both patient- and cohort-level feature contributions. Model updating will not be performed during initial validation; if performance drift or poor calibration is observed during prospective deployment, recalibration or updating will be conducted using prespecified procedures and reported transparently.

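### Complication predictions are meant to guide prophylaxis, but prophylaxis is not a named predictor, covariate or data item, so the model would estimate risk under existing care

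*Protocol article*

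**What the plan says.** **Intended use.** Interventions describes the model as "providing a noninvasive, accurate method for triaging endoscopy referrals and initiating prophylactic interventions". Proposed Solution says that the composite approach should "reduce unnecessary endoscopies while ensuring timely prophylaxis for those at greatest risk".

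**Outcome.** Under Outcomes, the second aim is to "identify patients at high risk of CSPH and early complications such as variceal hemorrhage or ascites". Participant Timeline and Data Collection add that clinical outcomes are followed through routine care over 24 months.

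**Model inputs.** Interventions: "This model will combine elastography metrics, platelet count, biochemical response trajectories, and comorbidity profiles, including AIH and MASH overlap". AI Model Development and Validation: "Candidate predictors will include longitudinal biochemical markers, platelet count, LSM, SSM, symptom scores, treatment response status, and relevant comorbidities". Neither list names a prophylactic drug or endoscopic therapy.

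**Treatment information.** For second-line PBC drugs, Eligibility Criteria states that "therapy class will be recorded as a covariate". No other treatment is given that role. Data Collection describes the retrospective source as "capturing historical laboratory values, elastography reports, and clinical outcomes relevant to PBC".

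**Eligibility.** Eligibility Criteria and Textbox 1 exclude Child-Pugh class B or C. They do not exclude known varices, existing CSPH or current prophylaxis.

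**Deployment.** AI Model Development and Validation adds that "if performance drift or poor calibration is observed during prospective deployment, recalibration or updating will be conducted using prespecified procedures".

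**The concern.** The treatment that the prediction is meant to prompt can itself change the outcome being predicted. If some high-risk patients in the development data receive prophylaxis and it prevents complications, they enter the data as non-events with an unfavourable profile. A model without prophylaxis among its inputs then attaches that lowered risk to the profile, and an untreated patient with the same profile is shown too low a figure. The decision to start prophylaxis needs the risk without it; the model supplies the risk under whatever care the cohort received.

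A related question arises in deployment. If the tool leads to effective prophylaxis, observed events fall below predicted ones. As worded, the recalibration statement does not separate that from a model that is wrong.

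**Working it through.** **1. The plan's own figure.** Sample Size and Power Considerations gives 600 participants and a CSPH prevalence of 24% to 47%. 600 × 0.24 = 144 and 600 × 0.47 = 282, which match the stated event counts. These are cases of CSPH itself, not later complications, so the mechanism examined here does not alter them.

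**2. What the model learns.** Let p be the untreated 24-month complication risk for a given profile, c the proportion of such patients on prophylaxis, and RR the relative risk of a complication under prophylaxis. A model that does not see prophylaxis learns

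learned risk = p × [1 − c × (1 − RR)],

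so the relative understatement is c × (1 − RR).

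**3. Inputs.** The documents give none of p, c or RR. All values below are assumptions: 1,000,000 simulated patients, mean untreated risk 13.6%, prophylaxis in a proportion c of the top 30% by risk and in 2% of the rest. Untreated risk in the top 30% is then 29.9%.

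| c in top 30% | RR | 1 − c(1 − RR) | Learned risk, top 30% | AUROC (0.782 with no prophylaxis) |
|---|---|---|---|---|
| 0.25 | 0.80 | 1 − 0.25 × 0.20 = 0.95 | 28.4% | 0.776 |
| 0.50 | 0.65 | 1 − 0.50 × 0.35 = 0.825 | 24.6% | 0.757 |
| 0.75 | 0.50 | 1 − 0.75 × 0.50 = 0.625 | 18.7% | about 0.72 |

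The understatement is 5%, about 17% and about 38% relative.

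**4. Sensitivity to the assumptions.**
- Low use and weak effect: c = 0.10 and RR = 0.8 give 0.10 × 0.20 = 2%; c = 0.30 and RR = 0.7 give 0.30 × 0.30 = 9%.
- No prophylaxis: c = 0 gives no bias.
- Only some events preventable: if prophylaxis affects a share s of the complications, the understatement is s × c × (1 − RR). With s = 0.5, the strongest scenario falls from 37.5% to 0.5 × 37.5% = 18.75%.

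The AUROC values above belong to this assumed complication outcome and say nothing about discrimination of existing CSPH.

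**The case against.** **A condensed article may leave the medication extract and the handling of treatment to the full protocol or SAP.** This is fair for the detail. Medical history is collected at baseline, the source is the EHR, and the predictor list is broad. The accurate statement is therefore that prophylaxis is not named as collected or modelled; a reader might infer that it will not be collected, and the text does not establish that. What remains is that the article does commit itself to two predictor lists, one treatment covariate and a recalibration trigger, and none of them provides for the treatment the tool is meant to guide.

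**Use of prophylaxis in the cohort is unknown.** This stands. A reader might infer that prophylaxis is expressly permitted and goes mainly to high-risk patients. The first would be read from the absence of an exclusion. The second is stated only as a goal of the future tool.

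**The headline targets concern CSPH.** This stands. One might infer that the AUROC is depressed against the 0.85 in Results, but that figure is for identifying CSPH, and preventing a bleed does not make a CSPH case a non-case.

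**Not every complication need respond to prophylaxis.** This stands and lowers the size. The follow-up lists name varices, ascites and hepatic encephalopathy, while hemorrhage appears only as an example under Outcomes.

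**Prophylaxis is a small part of the tool.** Partly. The order-set examples are pruritus, bone health and endoscopy referral, and Ethical Considerations leaves final decisions with the clinician. Yet starting prophylaxis is a stated use in two sections.

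**Harmful recalibration is speculative.** Largely so. A reader might infer that the rule would weaken a working tool. It refers to procedures that are not shown, and the pilot is a limited rollout in which a shortfall of 24-month events may not become visible.

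**Risk under current care is a legitimate target.** It is, if stated. The article does not say which risk is meant, and the stated use points to the other one.

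**Conclusion.** The point holds for the complication part of the Aim 2 outcome. As written, the plan yields complication risk under existing care, while the intended decision needs risk without new prophylaxis. Untreated risk is understated to the extent that high-risk patients in the cohort are treated effectively.

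The size cannot be derived from the documents. Under assumed coverage of 25% to 75% in the top 30% by risk and RR of 0.8 to 0.5, it is about 5% to 38% relative; it is smaller if only some complications respond, and negligible if prophylaxis is rare. Without dated prophylaxis records, the sponsor could not tell which case applies.

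Identification of existing CSPH, the 144 to 282 events and the 0.85 expectation are outside this finding.

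**What to change.** Results states that recruitment and analysis have not begun and that data collection is still to start, so these changes can be made before extraction.

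- **Data Collection:** extract start and stop dates of prophylactic drug and endoscopic therapy from the EHR, for the retrospective and prospective cohorts.
- **AI Model Development and Validation:** add prophylaxis at baseline as a candidate predictor.
- **Statistical Analysis:** state whether the target for complication outcomes is risk without new prophylaxis or risk under current care. Report a sensitivity analysis that censors at the start of prophylaxis with inverse-probability-of-censoring weights, beside the unadjusted version.
- **AI Model Development and Validation, deployment:** report calibration by prophylaxis status before any recalibration, so that fewer events in treated patients are not by themselves read as miscalibration.

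The cost is a small additional extract and one weighting model. The weighted analysis will have wider intervals and assumes no unmeasured reasons for starting prophylaxis. Under the assumed 13.6% risk, 600 patients give about 600 × 0.136 = 82 complications before the data are split, which is why weighting is proposed as a sensitivity analysis and not as the primary one. None of this changes or proposes a rule for giving prophylaxis.
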